## Background

Randomized clinical trials (RCTs) are the cornerstone of reliable evaluation of interventions in health care, with results that often impact clinical guidelines and evidence-based practice ultimately leading to better health care for patients [1–3]. However, conducting high-quality RCTs is challenging, resource intense, and associated with high costs [4, 5]. Tens of billions of dollars of public and private money are invested in RCTs every year, estimated to reach $68.9 billion a year by 2025 [6]. Moreover, RCT costs are rising. Over the last decade, a number of new initiatives and regulations were implemented to increase participant protection and to improve research quality [2, 7–10]. As a consequence, the complexity and administrative burden of RCTs have increased overall costs [11–15]. Furthermore, the implementation of medical advances, while highly desirable, has limited the incremental impact of new therapies, resulting in smaller beneficial effects of interventions, which requires larger RCT sample sizes [16, 17]. All these developments have resulted in escalating RCT costs, thus exasperating the problem of scarce resources for academic clinical research.

One consequence of these cost pressures is that the number of independent investigator-initiated RCTs has remained constrained over the last two decades [2, 18, 19] and a substantial proportion of these trials are prematurely discontinued due to recruitment and organizational problems [19], which risks many clinical research questions remaining unaddressed. Therefore, efforts to make investigator-initiated RCTs more cost-effective and sufficiently funded are urgently needed.

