## Study objectives and hypotheses

The aim of this study is to generate a database of detailed empirical resource use and cost data from 100 investigator-initiated RCTs in Switzerland, Germany, and the UK, so that we can descriptively investigate total RCT costs and proportions of total costs for individual cost items to achieve the following specific objectives:A)To investigate cost patterns on an absolute (actual costs in USD) and relative scale (% of total costs) including largest cost items for the whole RCT and for the planning, conduct, and finalization phases.B)To explore RCT costs across different strata including medical fields, intervention types, multicenter/single center status, and countries.C)To examine planned versus actual RCT costs and to explore factors that explain excess costs.D)To explore hidden costs associated with conducting an RCT such as resource use and costs for writing the protocol, trial committees, ongoing communication, and managing serious adverse events (SAEs).

We have the following specific hypotheses:(i)The expenses for participant recruitment and follow-up typically constitute the largest proportion of total RCT costs.(ii)Data monitoring constitutes—on average—less than 15% of total RCT costs.(iii)Delays in recruitment of trial participants explains most of the excess costs.(iv)Cost structures (proportions) and fixed cost items (e.g., regulatory or ethics committee approval) are similar across medical fields and countries.

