From protocols and publications, we will extract the relevant RCT baseline characteristics. These will include medical field (indication), type of intervention and control group, use of placebo, number of arms, type of patient population, specific trial design (e.g., cross-over or factorial design), number of trial arms, number of trial sites, planned and achieved sample size, originally planned total costs and planned budget (if available), primary outcome(s), trial duration, planned and actual recruitment duration, monitoring method, electronic or paper-based data capture/case report forms, and funding sources.

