### Sample size considerations

We simulated data sets with various numbers of RCTs to study how many RCTs we would need to achieve a 90% probability (statistical power) for a sufficiently narrow 95% confidence interval (CI) around the estimated mean cost proportions for individual cost items. We assumed that a 95% CI width of 6% (i.e., a maximum of ± 3%) for the estimated mean would be sufficiently precise. The confidence interval assumes a normal distribution and is calculated as 1.96 * the standard error. Figure 1 shows how the required sample size depends on the true average proportion. Note that there are two lines: a dark line for a rather wide assumed distribution of proportions (tau = 10; beta distribution with a precision of 10) and a gray line for a plausible, narrower distribution (tau = 20). According to the dark line (the wider distribution), including a total of 60 RCTs would suffice to achieve a power of 90% to find a satisfyingly narrow 95% CI of 6% for a mean proportion below 0.15. Thus, our original plan was to include at least a total of 180 RCTs which appeared appropriate to achieve sufficient precision for estimated proportions (even within subgroups such as countries). However, it proved extremely challenging to find principal investigators willing to share detailed resource use and cost data of their trials rendering the target sample size of 180 RCTs unfeasible. Therefore, we reduced our target to 100 RCTs (Switzerland *n* = 60; Germany *n* = 20; UK *n* = 20). This number is feasible and will still allow for sufficient precision of unstratified estimates and to conduct multivariable regression analyses without overfitting models.

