### Statistical analysis

We will calculate proportional contributions to total costs for individual cost items and for the three pre-defined study phases (preparation, conduct, and finalization). Proportions across RCTs will be summarized with descriptive statistics accompanied by 95% CIs. We will summarize total resource use (working hours and costs), as well as resource use and costs for individual cost items, and costs per patient using descriptive statistics (means or medians accompanied by standard deviations (SDs) or 25th to 75th percentile ranges [IQRs] according to the distribution, minimum [min] and maximum [max], respectively) overall and stratified by RCT over- or under-budget (± 10%), medical field, intervention type, country, and pilot vs non-pilot RCTs (objectives A–D).

We will categorize reasons for going over- or under-budget as reported by trial investigators and reasons for prolongation of recruitment [43] (objective C). In sensitivity analyses, we will calculate results without adding 30% of unaccounted time and/or adding overhead costs. We will not exclude any collected data from planned analyses. Outliers will be reviewed and checked/verified with principal investigators of included trials.

We will conduct two multivariable linear regression analyses with total costs in US dollars and total costs per patient as dependent variables [44]. Medical field, country, number of trial sites, actual sample size (only in regression model for total costs), routine data use, intervention type, and actual trial duration will be used as independent variables in both regression analyses. As for the investigation into the strata of cost proportions of RCTs across medical fields, intervention types, and countries, we will first plot distributions of cost proportions graphically stratified by medical field, intervention type, and country. For each RCT, we will descriptively compare the originally planned versus actual total costs, the originally planned versus actual recruitment duration, and the planned versus actual sample size (objective C).

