We will calculate excess costs for each RCT (delta of originally planned total costs and actual total costs [Total costs − Planned Costs]). This will help investigate trial characteristics associated with excess costs of an RCT (dependent variable). We will develop a multivariable regression model with delta in recruitment duration, actual sample size, and actual number of trial sites, country, intervention type, and medical field as independent variables (objective C).

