#### Missing data

Throughout the study we will be in direct contact will principal investigators and all data entry will be followed by a detailed cost report and interview. As such, we do not anticipate missing data. Nevertheless, some investigators may not have calculated an initial budget for their trials, i.e., in these cases we will document missing budgets and for analyses in which initial budgets are considered we will conduct complete case analyses. If income was not provided by the institution to calculate billable hours, we will impute the median income for the respective country, for each specific team role.

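### The excess-cost regression measures cost and recruitment time against plan but sample size only as achieved, so the delay coefficient is distorted, in either direction, whenever delay and shortfall are correlated

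*Protocol article*

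**What the plan says.** The Statistical analysis section of the protocol article defines the dependent variable as the "delta of originally planned total costs and actual total costs [Total costs − Planned Costs", a departure from plan. It then names the covariates: a "multivariable regression model with delta in recruitment duration, actual sample size, and actual number of trial sites, country, intervention type, and medical field". Recruitment duration is thus also a departure from plan, whereas sample size and number of sites enter at their final values.

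Planned sample size is available. The Data collection procedures section lists "planned and achieved sample size, originally planned total costs and planned budget (if available" among the extracted items. Its only stated use against achieved size is descriptive: for each trial the authors will compare "the originally planned versus actual recruitment duration, and the planned versus actual sample size (objective C").

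The third hypothesis, under Study objectives and hypotheses, reads "Delays in recruitment of trial participants explains most of the excess costs". The excess-cost model is the only multivariable analysis in the article that contains recruitment delay.

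**The concern.** A trial's cost departs from its budget partly because the trial ran longer than planned and partly because it treated fewer patients than planned. Achieved size does not capture the second part. One hundred patients may be a fully recruited trial of 100 or a trial of 200 that stopped at half, and only the second saved money against its budget. A trial that closed on its planned date with 60% of its patients has zero delay and a saving that no term in the model represents.

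Slow accrual can lead to extension, to a shortfall, or to both, so delay and shortfall may well be correlated. The saving left in the error term is then partly attributed to delay. This is ordinary omitted-variable bias, and more trials do not remove it. At stake is how the delay coefficient is read when the authors report which factors explain excess cost and comment on the third hypothesis.

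The situation is plausible for these trials: the Background says that "a substantial proportion of these trials are prematurely discontinued due to recruitment and organizational problems", and the eligibility criteria do not exclude trials that missed their target.

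**Working it through.** The article gives no figure for this regression, so there is none to reproduce. The check has an algebraic part and a simulated part.

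**Inputs from the article.** Outcome and covariates as above. At most 100 trials: "Therefore, we reduced our target to 100 RCTs (Switzerland *n* = 60; Germany *n* = 20; UK *n* = 20"). Fewer will enter this model, because "for analyses in which initial budgets are considered we will conduct complete case analyses".

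**Inputs assumed, because the article does not give them.** Cost per patient, cost per month of delay, the relation between delay and shortfall, the residual spread, and the number of trials with a budget (80).

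**Algebra.** Suppose, relative to plan,

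excess = a + ct × delay − cn × shortfall + error.

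If shortfall is left out, the fitted delay coefficient tends to ct − cn × b. Here b is the slope of shortfall on delay, given the covariates that remain. With cn positive, b > 0 pulls the coefficient down, b < 0 pushes it up, and b = 0 leaves it alone.

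**Simulation relative to plan** (3,000 replicates, 80 trials):
- Planned size lognormal, log-SD 0.8.
- Accrual-rate ratio r lognormal, median 0.7, log-SD 0.3, clipped to 0.3–1.
- A share x of the accrual problem is met by extending: delay = x(1 − r)/r, shortfall = (1 − r)(1 − x).
- Excess = 0.10 + ct × delay − cn × shortfall + N(0, 0.15).
- The planned model uses delay and log achieved size. The amended model uses delay, shortfall and log planned size.
- Sites and the categorical covariates are left out here. The dollar-scale check below includes them.

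Results for ct = cn = 0.35:

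| How slow trials react | Delay-shortfall correlation | b | Planned model | Amended model |
|---|---|---|---|---|
| Nearly all split it about half and half (x near 0.5) | 0.76 | 0.33 | about 0.23 | 0.35 |
| x spread evenly over 0–1 | about 0 | 0.01 | 0.35 | 0.35 |
| Each extends fully or stops on time, 50:50 | −0.48 | −0.22 | 0.43 | 0.35 |

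The formula agrees: 0.35 − 0.35 × 0.33 = 0.23, and 0.35 + 0.35 × 0.22 = 0.43.

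Other cost shares give the same pattern. With ct = 0.20 and cn = 0.50, the planned model gives about 0.04, 0.20 and 0.31 in the three rows. With ct = 0.50 and cn = 0.20 it gives 0.43, 0.50 and 0.54. The amended model returns the true value each time.

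**Simulation in dollars** (1,000 replicates, 100 trials; sites, country, intervention type and medical field included; true delay effect 10 thousand USD per month; residual SD 100 thousand USD; median planned size 200). Delay coefficient under the planned covariates, by assumed cost per missing patient:

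| Latent delay-shortfall correlation | 1 thousand USD | 3 thousand USD | 5 thousand USD |
|---|---|---|---|
| 0.5 | 6.5 | −0.3 | −7.1 |
| 0 | 10.1 | 9.9 | 9.9 |
| −0.5 | 13.5 | 20.3 | 26.9 |

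With achieved minus planned size, or with planned size added to achieved size, the mean is 9.9 to 10.1 throughout. With 70 trials the means are essentially the same.

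**Precision.** In the most collinear case of the relative-to-plan simulation, the standard error of the delay coefficient rises from about 0.08 to 0.12 when shortfall is included.

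**The case against.** Four arguments on the other side deserve weight.

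1. **Direction.** A reader might infer that the planned model always hides the cost of delay. The documents do not support that. If trials in trouble either extend or close on time, delay and shortfall are negatively correlated and the coefficient is too large, which would favour the third hypothesis. The trial that closes on its planned date with 60% of its patients is of this kind. This objection stands.

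2. **Size.** A reader might also take a fixed percentage from the simulation. The downward case needs nearly every slow trial to divide its problem about equally (correlation 0.76), and the cost shares, accrual distribution and residual spread are all assumed. Eligible trials must be completed or nearly so, and the authors themselves expect their sample to lean towards successful trials, so shortfalls may be rarer here than in the wider population. This stands too.

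3. **Link to the third hypothesis.** The article ties the regression to objective C and assigns no coefficient or threshold to the hypothesis. Explaining most of the excess is a statement about share, which a slope does not measure by itself. Reported reasons for budget deviation and prolonged recruitment, and the descriptive plan-versus-actual comparison, also inform it. So this coefficient is not the test of the hypothesis, although it is the only multivariable evidence that bears on it.

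4. **Estimand.** If the aim were the net cost association of delay as trials actually handled it, savings from fewer patients would belong in the coefficient. The article states no such aim. Even under it, achieved size is not the covariate one would choose, and savings in trials that closed on time remain unexplained.

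None of these removes the inconsistency: a from-plan outcome is modelled with a from-plan duration and a size term that carries no reference to plan.

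**Conclusion.** The point holds in conditional form. As specified, the model omits the cost saved by patients who were budgeted but not recruited, so its delay coefficient cannot be read with confidence. The coefficient is distorted whenever delay and shortfall are correlated and fewer patients cost less. The direction follows the sign of that correlation, and there is no distortion if it is zero.

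The magnitude cannot be derived from the documents. On the assumed equal cost shares, a true 0.35 is estimated as about 0.23 to 0.43 over correlations from 0.76 to −0.48. In relative terms that is (0.23 − 0.35)/0.35 = −34% to (0.43 − 0.35)/0.35 = +23%. These figures illustrate the mechanism and do not predict this sample. The model is exploratory, but the article itself fixes the covariate list and the remedy uses data already collected, so the change should be made.

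**What to change.** In the excess-cost regression in the Statistical analysis section, replace achieved sample size by two terms: achieved minus planned sample size (or percent of target reached), and planned sample size as the measure of scale. Report the delay and shortfall coefficients together, and state that the delay coefficient is then the association at a given shortfall.

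The change takes one or two sentences, needs no new data and adds one parameter. Its price is a wider interval for delay when delay and shortfall are strongly correlated (standard error about 0.08 to 0.12 in the simulated case).

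Number of sites has the same plan-versus-actual mismatch. No change is proposed there, because a planned number of sites is not among the variables the article lists for extraction.

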#### Missing data

Throughout the study we will be in direct contact will principal investigators and all data entry will be followed by a detailed cost report and interview. As such, we do not anticipate missing data. Nevertheless, some investigators may not have calculated an initial budget for their trials, i.e., in these cases we will document missing budgets and for analyses in which initial budgets are considered we will conduct complete case analyses. If income was not provided by the institution to calculate billable hours, we will impute the median income for the respective country, for each specific team role.

#### Changes to the original OSF registration

In our initial OSF registration, we had planned to include an additional sample of Canadian RCTs. Due to feasibility issues in Canada and lack of support from collaborators, we needed to exclude the country. Furthermore, it was challenging to find principal investigators willing to share their cost data, as such we decided to expand our scope and include a small sample of pilot studies (*n* = 10) and RCTs initiated in Switzerland but conducted in low- and lower-middle-income countries (*n* = 10). In addition, we initially did not want to include trials published later than 5 years; this was extended to 10 years to increase our sample of eligible RCTs.

### Confidentiality

We will inform principal investigators of included trials that only aggregated data will be published and none of the individual RCTs, investigators, staff members, or sponsors will be identifiable. A standard data sharing agreement was consented to by both parties. If required by the institution, a more detailed data sharing agreement was written and signed by both departments. The data was stored on a secure online database (REDCap) and stored on a safe University Hospital Basel server. Access to this database is limited and password protected. PIs only had access to their data entry form.

## Discussion

This empirical study will help guaranteeing the sustainability of investigator-initiated RCTs in the future. The Making Clinical Trials more Affordable (MARTA) working group has prepared for the present study with previous projects: An interview study published by McLennan et al. shed light on the systemic underfunding of investigator-initiated clinical trials in Switzerland, identifying inaccurate budget estimations and limited funding sources as key challenges [45]. The authors highlight the need for transparency on trial costs as well as training in budgeting practices [45]. Another study explored the use of electronic health records and their potential for cost reduction by supporting recruitment and outcome assessment in RCTs [46]. A scoping review has systematically identified several freely available tools for planning and monitoring of RCT costs, emphasizing the need for user-testing and validation of tools [47]. Additionally, a meta-research study investigated the challenges in obtaining placebos, highlighting the substantial resources required [48]. Together, these studies contribute to the ongoing conversation on optimizing the planning, funding, and execution of clinical trials for more affordable and effective research practices. Nevertheless, empirical data on RCT costs of investigator-initiated RCTs are still missing and urgently needed. The present effort will help identify areas for cost reduction, improve future funding of RCTs, and will help investigators plan their trials by providing real cost and time expenditure estimates.

As a major strength, this study will be the first of its kind to use activity-based costing to systematically and empirically investigate the resource use and costs of RCTs in Germany, Switzerland, and the UK. However, the study also has limitations. Firstly, despite including trials from different medical fields and countries, our findings may not be generalizable to all types of trials or research settings, as the costs can vary widely depending on the research question, therapeutic area, and location. Secondly, we will collect self-reported retrospective data from investigators and their teams, which may introduce reporting bias and inaccuracies. Especially the variable costs (time expenditures) are not usually recorded on site and need to be estimated by the principal investigator and study team members. Thirdly, RCTs of principal investigators who agreed to share the resource use and cost data with us might not be representative of all RCTs, but could be a selection of more successful RCTs compared with those for which principal investigators did not share cost data. We will keep a list of all contacted trial investigators, who do not wish to participate in our study, and will extract characteristics of corresponding not-included RCTs from trial registries and publications to enable a comparison of RCT characteristics. Fourth, our sample only includes trials conducted in Europe and costs may differ in North America or Asia because of differences in healthcare systems, medical research, and health insurance policies. Lastly, our research does not investigate if the different monitoring strategies have an influence on data quality.

Future research should consider alternative methodologies such as prospective data collection to provide more accurate cost estimates.

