### Eligibility criteria and trial identification

RCTs will be included if they have been completed or are close to completion (statistical analysis ongoing or manuscript in preparation). Trials will be excluded if they are industry sponsored, dose-finding RCTs, RCTs primarily evaluating pharmacokinetics or physiology, include healthy volunteers, or RCTs that published results more than 10 years prior to the start of this investigation. To enhance comparability across countries, we will aim to include 10–15 RCTs each from cardiovascular, oncology, surgical, and miscellaneous fields. However, it was challenging to find principal investigators willing to share their cost data, as such we decided to expand our scope and include a small sample of pilot studies (*n* = 10) and RCTs initiated in Switzerland but conducted in low- and lower-middle-income countries (*n* = 10).

We will identify potentially eligible RCTs using two approaches: Firstly, we will use a convenience sample and contact Clinical Trial Units (CTUs), trial networks, and individual principal investigators known to the authors in all three countries and ask them about eligible investigator-initiated RCTs they could contribute. Most of our direct trialist connections are in Switzerland. In particular, we will approach the Swiss CTU network; the KKS Network, UK Registered CTUs Network; Network of Hubs for Trials Methodology Research (UK); UK Trial Managers’ Network, Trial Forge Initiative (UK); Koordinierungszentren für Klinische Studien Network (DE); Oncology network (DE); and the Clinical Trials Centre Cologne (DE).

Secondly, we will screen trial registries for completed RCTs and then invite principal investigators to participate in our study. These trial registries will include clinictrials.gov, the ISRCTN registry, the Health Research Authority (NHS) registry, Kofam (Swiss Clinical trial registry), and the Deutsches Register Klinischer Studien (DRKS; the German clinical trial registry).

For each RCT contributed to the project, we will offer the trial teams 200 euros as a compensation for their efforts.

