### Data collection procedures

Protocols and publications will be collected for each of the RCTs and the cost data will be collected and stored in the electronic data capture system REDCap [33, 34]. Trial teams will enter their cost and resource data directly into an online data collection form. Data entry will be followed by a short interview to clarify unclear values and missing data. A cost report will be generated for each trial, which is then reviewed by the trial team. Funders of RCTs were not contacted, since previous research has shown that budgets are purposefully underestimated and we wanted to record the actual costs of RCTs [35].

For the collection of the resource use and cost data, we will use a previously developed and tested cost item list developed by Speich et al. that follows principles of activity-based costing [27, 36]. An overview of the collected variables can be found in Table 1. All variables and the online data collection form can be found in the supplementary material (Supplement Table 1 and Supplement Table 2). The online cost report form will be tested on two RCTs and changes will be made based on the feedback provided by investigators and study teams.

**Table 1 Tab1:** Total trial costs

**Total Trial Costs ** • Trial Budget • Trial Funding • Total trial costs • Total trial costs adjusted for employer contributions • Total trial costs adjusted for employer contributions and 30% unaccounted time • Total trial costs adjusted for employer contributions, 30% unaccounted time and overhead		
**Planning**	**Conduct**	**Finalization**
**Fixed Costs** • Ethics Committee approval fees • Health authority fees • Other approval fees • Costs for Infrastructure and Equipment • Shipping costs • Insurance fees	**Fixed Costs** • Advertisment • Costs of Intervention • Placebo manufacturing • Additional procedures and material • Patient reimbursement • Specimen analysis • AE/SAE/SUSAR material • Travel costs • Audits and Inspections	**Fixed Costs** • Publication fees • Conference fees and costs

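### The comparison meant to check participation bias is defined by refusal, which is narrower than the non-contribution it is meant to examine; read literally, it omits investigators who never replied

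*Protocol article*

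**What the plan says.** The third limitation in the Discussion says that the contributing RCTs might not be representative and "could be a selection of more successful RCTs compared with those for which principal investigators did not share cost data". The safeguard follows in the next sentence: "We will keep a list of all contacted trial investigators, who do not wish to participate in our study", after which the authors "will extract characteristics of corresponding not-included RCTs from trial registries and publications to enable a comparison of RCT characteristics".

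Two recruitment routes are described under Eligibility criteria and trial identification. In the first, "we will use a convenience sample and contact Clinical Trial Units (CTUs), trial networks, and individual principal investigators known to the authors". In the second, "we will screen trial registries for completed RCTs and then invite principal investigators to participate in our study". Data collection procedures then sets out three steps for a team that agrees: online entry, an interview, and the team's review of a cost report.

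Sample size considerations reports that "it proved extremely challenging to find principal investigators willing to share detailed resource use and cost data of their trials". This is the reason given there for lowering the target from 180 to 100 RCTs.

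**The concern.** The warning and the safeguard concern different groups. The warning is about every RCT for which no cost data were supplied. The safeguard covers RCTs whose investigators were unwilling. Someone who does not answer an invitation has supplied no data but has expressed no unwillingness. The same holds for a team that agrees and then does not deliver.

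Participation was hard enough to obtain to change the sample size and widen the scope, and this comparison is the only check on selective participation that the article states. If it rests on refusals alone, a reader cannot tell whether similarity between the two groups says anything about the other non-contributors. Because only aggregated data will be shared, outside readers could not rebuild the comparison from the study's own contact records.

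**Working it through.** **Step 1: the two definitions side by side.**

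| | Group | Place |
|---|---|---|
| Bias feared | RCTs whose investigators supplied no cost data | Discussion, third limitation |
| List kept | Contacted investigators unwilling to take part | Discussion, next sentence |
| RCTs extracted | Not-included RCTs corresponding to that list | Same sentence as the list |

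The phrase for the extracted RCTs sounds broad, but the word *corresponding* ties it back to the list, so it does not widen the group. The first group contains the second. What lies between them is non-response, and agreement without delivery.

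**Step 2: can that remainder be other than empty?** For non-response, yes: investigators found by registry screening are invited, and silence is an ordinary result of an invitation. For agreement without delivery it is possible, since several steps follow agreement, but the article reports no such case.

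**Step 3: what can be counted.** Study status gives 43 + 20 + 16 + 8 = 87 RCTs with data collected, which adds up. No number contacted, refusing, silent or not completing is given. No response rate follows from the article, and there is no planned figure to reproduce.

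**Step 4: illustration on assumed inputs.** Take a trait such as early discontinuation. Let p_inc, p_dec and p_sil be its frequency in included RCTs, in declining RCTs, and in silent or non-completing RCTs. Let s be the share of non-contributors who are silent or did not complete.

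- Gap seen = p_dec − p_inc
- Full gap = (1 − s) × p_dec + s × p_sil − p_inc

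With p_inc = 20% throughout:

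| p_dec | p_sil | Gap seen | Full gap, s = 0.2 | s = 0.5 | s = 0.8 |
|---|---|---|---|---|---|
| 20% | 30% | 0 | 2 | 5 | 8 |
| 20% | 40% | 0 | 4 | 10 | 16 |
| 40% | 40% | 20 | 20 | 20 | 20 |
| 40% | 20% | 20 | 16 | 10 | 4 |

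(Gaps in percentage points. Example, second row, s = 0.5: 0.5 × 20 + 0.5 × 40 − 20 = 10.)

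The first two rows hide a difference, the third shows it correctly, and the fourth overstates it. None of these inputs comes from the article. The table shows only that the refusal-only gap does not determine the full gap.

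**The case against.** The strongest reply is that this is one loosely worded clause in a limitations paragraph. The preceding sentence names all non-sharers, and a sympathetic reader could take unwillingness to include silence. Nothing says that non-responders are excluded. That is fair, and the authors may intend the wide group. But the clause states a rule, and two teams following it could build different comparison groups. The ambiguity lies in what is written, so it is not a detail left to a fuller document.

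It is also true that the article claims no representativeness. It calls its first route a convenience sample and warns of selection itself. The comparison feeds no estimate or weight, so the cost results do not depend on it. Both points stand and limit the weight of the concern.

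Three stronger readings are tempting but not supported:

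- **Unfinished forms entering the totals.** A reader might infer this from "We will not exclude any collected data from planned analyses". That sentence stands next to the one on verifying outliers and most naturally concerns extreme values. Data collection procedures adds "Data entry will be followed by a short interview to clarify unclear values and missing data" and a team-reviewed cost report, and Missing data repeats that all entries go through a report and interview. No abandoned entry is reported.
- **Trials that clinical trial units did not put forward.** These may never have been known to the authors. A list of contacted investigators could not capture them under any wording.
- **A stated share of non-contributors left unexamined.** Any such percentage would merely restate an assumed refusal share.

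**Conclusion.** The concern holds as a mismatch of definitions: the stated comparison group is narrower than the group whose absence it is meant to examine. On the literal wording, non-responders are omitted, as is anyone who agreed but did not deliver. Size and direction cannot be determined, because the article gives no contact, refusal or non-response numbers. A reader might infer that the comparison is bound to make the sample look representative. The article does not support that, since the error can run either way or be nil, and the authors make no such claim.

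The conclusion rests on reading the clause as written and on non-response having occurred among those invited, which is likely but not documented. It does not affect the cost analyses themselves. It affects whether the one stated check on participation can be interpreted, and it is worth correcting for that reason.

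**What to change.** Reword the sentence in the Discussion so that the comparison group is every contacted eligible RCT that did not contribute cost data. Count three categories separately: declined, no reply, and agreed but not completed. For all of them, extract those baseline characteristics listed under Data collection procedures that are publicly available, such as medical field, number of sites, planned and achieved sample size, and trial duration, together with country. If non-responders are many, a random sample of them is enough, provided that it is reported as such.

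The sources are the registries and publications already planned for this comparison, so the cost is additional extraction time and a change of wording. As 87 RCTs had been collected by December 2023, the contact records should be classified soon, while the outcome of each contact can still be recovered.
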